### Pure tone audiometry (PTA)

Audiometry 125 to 14,000 Hz is performed using the single-interval adaptive procedure (yes/no method) implemented in multiThreshold [56, 57]. The starting value for the target tone is at 30 dB SPL, with target duration of 250 ms.

The procedure consists of changing the level of the stimulus from trial to trial using a one-down, one-up adaptive procedure [57]. The start level is randomly located in a range 10 dB to the start value. After the first no-response, the stimulus level is set to the mid-point between the previous two levels. The procedure then continues with a reduced step size of 2 dB.

Catch trials serve to check that the participant understands the instructions. The rate of catch trials starts at 0.2. At the beginning of a run, the catch trial rate is 0.2 (20%). If the participant is caught out, the rate is increased on the next run in steps of 0.1. If the subject is not caught out on a run, the rate is reduced progressively to the minimum rate.

### Loudness discomfort level (LDL)

The LDL is used to measure the loudness at which external sounds become uncomfortable [58] and is a valid clinical measure for characterizing the “threshold of discomfort.” The participant will evaluate according to their personal perception whether they find the loudness of the sound pleasant, loud, or unpleasant. As soon as it is selected as being unpleasant, the discomfort threshold is reached, which completes a run.

The measurement is performed in each ear separately, with a PT of 500 ms at frequencies of 500, 1000, 2000, and 4000 Hz [59]. The starting level is at 75 dB and is then raised by 3 dB with each trial until the subject declares the tone is uncomfortable. The trial is then stopped, and the next trial initiated.

### Isometric forward masking contour (IFMC)

The forward masking is a technique for inferring human cochlear compression [60], and the technique is also used to detect the occurrence of subjective tinnitus as a result of cochlear damage [61, 62].

The supra-threshold measure of frequency selectivity is assessed using a forward masking procedure. A forward masking task identifies the maximum loudness level of masking tone at which the probe tone presented immediately after can still be heard, and at which the target tones are preceded by masker tones. The masker level is varied adaptively between trials to identify the masked threshold, in order to produce an isometric forward masking contour (IFMC) [63].

The initial target level is set to 35 dB for both frequencies. The parameters of the paradigm consist of target tones of 16 ms at the two frequency conditions multiplied with the factors 0.5, 0.7, 0.9, 1, 1.1, 1.3, and 1.6 preceded by a masker tone of 108 ms, with a silent gap of 30 ms in between. Thus, the participant will hear clicks (probe tones) and beeps (masker tones). The participants should report whether or not they heard the probe tone during the measurement [63, 64].

### Temporal masking curve (TMC)

The test is used to estimate auditory compression using a forward masking paradigm. The gap between the masker and the probe is varied between measurements while the frequency is held constant. A fixed-level target follows a masker tone and the audibility of the target is manipulated by changing the level of the preceding masker. Then, the masked thresholds generate a temporal masking curve (TMC) [63, 64].

For the TMC, the starting level of 50 dB is used at the frequencies of 500 Hz and the tinnitus frequency. The target stimulus is 20 ms, preceded by a 108-ms masker. The gap between the masker and the target varies between runs over a range of 5, 10, 20, and 40 ms.

### Sensation level (SL)

The SL is performed in a diotic form, with stimuli of 75 ms. The starting level is 30 dB and the stimuli are related to target frequency of 500 Hz and the individual tinnitus frequency, determined previously through matching. The procedure is similar to that used to determine the hearing threshold (PTA), but only the two specific frequencies are used.

## Tinnitometry

Tinnitometry comprises a battery of tests as pitch matching (PM), minimal masking level (MML), and residual inhibition (RI) measurement [65].

The audio system used for the tinnitometry is a custom software tool made in MAX 8 (Cycling’74, USA), using Babyface Pro FS sound card (RME Fireface UCX; Audio AG, Haimhausen, Germany), and headphones model AKG K271 MK II (AKG Acoustics, Northridge, USA), with a hardware controller Novation Nocturn USB Midi (Novation, UK) to manipulate parameters.

### Pitch matching (PM)

In the PM procedure, the participant identifies an external sound which is most similar to the subjective perception of the tinnitus. The procedure is performed using the method of adjustment [29, 66] with the same modifications described in [67].

The tinnitus frequency is identified in the ear contralateral to the tinnitus in unilateral cases, or in the better-hearing ear in cases of bilateral tinnitus [68]. The starting frequency is chosen from the audiogram and corresponds to the frequency with the highest hearing loss in each ear. The participant is then instructed to adjust the frequency to the pitch of their tinnitus, which ranges from 30 to 18,000 Hz. After identifying the frequency, the loudness is adjusted. The participant manipulates the knob corresponding to the sound intensity until they judge that the intensity emitted by the equipment is equal to that of their tinnitus.

The next step is to perform the octave confusion test. The selected frequency is compared to a frequency one octave higher and one octave lower, with the aim of confirming the frequency chosen.

To ensure reliability of the pitch matching, the test is repeated twice, and the frequency, which is matching the subjective tinnitus perception better, is chosen for further procedures.

### Minimum masking level (MML)

The MML measures the level of sound needed to cover the perception of tinnitus. It is adjusted to the lowest level of noise (white noise—WN) until tinnitus is thoroughly masked, in a diotic presentation [65, 69].

### Residual inhibition (RI)

RI is a temporary reduction of tinnitus following the cessation of masking sounds. RI measurement is performed using WN sound presented at MML + 10 dB level [30, 66]. The procedure is performed diotically.

After stimulation offset, the participants are asked to rate the change in tinnitus intensity right after the offset on a scale of − 5 (totally disappeared), 0 (same level), or + 2 (much louder).

### Criteria for discontinuing or modifying allocated interventions {11b}

Given the general low risk associated with the study procedures, no realistic scenario of withdrawal or discontinuation can be drawn for this study. Although risk is not commonly reported with the current therapy, participants will be monitored in case they experience any symptoms. The probability exists for some minor side effects exists, as reported in the literature, such as nausea, tingling, headache, tiredness or irritating sensation, difficulty in concentration, redness, or pain [18].

In any case, participants may terminate their participation in the study at any time and without any justification. They will be registered as dropouts and will not be taken into account in the analysis.

All participants will be informed in writing on the information sheet and on the informed consent form, and verbally in the interview prior to enlisting in the study, that they may terminate their participation in the study at any time and without justification. After withdrawal, the participants will be contacted for a debriefing interview. Dropouts will be replaced in order to achieve the intended sample size whenever possible. Replacement will be performed along the established selection and allocation criteria.

Compliance is usually high, as has been observed in former studies of our group [70, 71], and other groups in the field of tinnitus research. This is true even in the absence of monetary incentives and possible detrimental effects on the condition. Therefore, no specific measures are considered to increase compliance.

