#### Dropout criteria

The dropout criteria are participants who discontinue the study without justification.

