### Sample size {14}

Sample size calculations were conducted in G*Power 3.1.9 for the repeated measures, within-between interaction (ANOVA). The total sample size needed to detect a high assessment-by-treatment interaction effect (*f* = 0.25, beta = 0.95, alpha = .05, groups = 2, measurements = 5) is 32 participants. However, to compensate for a high estimated dropout rate of up to 25% during treatment, the aim is to recruit 40 participants leading to 20 participants per group.

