#### Primary analysis

The data will be statistically analyzed for changes in subjective tinnitus loudness and distress (VAS) and MML by means of frequentist linear mixed-effect modelling (LME) by the biometrician after data collection has been completed.

Between- and within-subjects repeated measures ANOVA will be used to compare the effect of treatment pre and post, in both intervention groups.

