### Methods in analysis to handle protocol non-adherence and any statistical methods to handle missing data {20c}

Efficacy analyses will be performed according to the intention-to-treat principle. The participants will be analyzed in the treatment arms to which they were randomized, irrespective of whether they refused or discontinued the treatment, or whether other protocol violations occurred. Since the questionnaires are collected electronically and each item is mandatory for questionnaire completion, we expect a low number of missing data. The other self-report assessments are also carried out electronically by standard, so that the number of missing data should also be low here. Should missing data nevertheless occur, this will be handled as follows:

The missing numerical data will be filled according to the average value of all participants or a more fitting procedure of data imputation depending on the specific issue (e.g., median or *k* nearest neighbor). Non-numerical missing data are listed as missing data accordingly.

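### The protocol promises intention-to-treat but elsewhere excludes and replaces everyone who leaves, and does not say which rule governs the primary analysis

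*Protocol article*

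**What the plan says.** Four places in the protocol article bear on who is analysed.

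- **Dropout criteria:** "The dropout criteria are participants who discontinue the study without justification".
- **Criteria for discontinuing or modifying allocated interventions {11b}:** participants may stop at any time without giving a reason. Of those who do, it says: "They will be registered as dropouts and will not be taken into account in the analysis". It then adds: "Dropouts will be replaced in order to achieve the intended sample size whenever possible". Replacements enter under the same selection and allocation criteria.
- **Methods in analysis to handle protocol non-adherence and missing data {20c}:** "Efficacy analyses will be performed according to the intention-to-treat principle". Participants stay in their randomised arm "irrespective of whether they refused or discontinued the treatment, or whether other protocol violations occurred". For gaps in the data it says: "The missing numerical data will be filled according to the average value of all participants or a more fitting procedure of data imputation".
- **Primary analysis:** VAS loudness, VAS distress and MML are analysed "by means of frequentist linear mixed-effect modelling (LME) by the biometrician after data collection has been completed". No analysis set is named.

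The Sample size section plans for dropout of up to 25% during treatment and raises the target from 32 to 40 participants, 20 per group.

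**The concern.** Item 20c keeps randomised participants who discontinue. Item 11b removes those who leave and fills their places. An analyst cannot apply both to the same leaver, and the article does not say which rule prevails. The analysis set could therefore be settled after the pattern of dropout is known.

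This matters more than usual here. Two of the three primary outcomes are self-rated, and the schedule runs to 26 sessions. It is plausible, though the article gives no data on it, that those who feel no benefit or notice side effects are likelier to stop. Excluding them would make membership of the analysed set depend on response. Replacement restores the head count but not the randomised comparison.

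The crossover adds a second cost. A participant who leaves in the second block has already supplied a full first block. Item 11b discards those data, although a linear mixed model can use incomplete series.

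**Working it through.** **1. The rules side by side**

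| Situation | Item 20c | Item 11b |
|---|---|---|
| Stops stimulation, keeps attending | Analysed as randomised | Not addressed explicitly |
| Leaves the study in block 1 | Analysed as randomised, on the natural reading of intention-to-treat | Excluded, replaced |
| Leaves in block 2 with block 1 complete | Analysed as randomised, on the same reading | Excluded, replaced; block 1 data lost |

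The second and third rows conflict. Only the first can be read without conflict.

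**2. The plan's own sample size**

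The plan states "0.25, beta = 0.95, alpha = .05, groups = 2, measurements = 5) is 32 participants". The value printed as beta is read as power. The correlation among repeated measures (ρ) and the sphericity correction (ε) are not stated; I assume ρ = 0.5 and ε = 1.

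- λ = f² × N × m / (1 − ρ) = 0.0625 × 32 × 5 / 0.5 = 20.0
- df1 = (2 − 1)(5 − 1) = 4; df2 = (32 − 2)(5 − 1) = 120
- Power = 0.957, and 32 is the smallest even N reaching 0.95. The figure reproduces.

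**3. How many participants the conflict touches**

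- Ceiling: 0.25 × 40 = 10 randomised participants.
- Left before replacement under item 11b: 40 − 10 = 30, against the 32 required.
- Power at N = 30: λ = 0.0625 × 30 × 5 / 0.5 = 18.75, df2 = 112, power 0.943. Over ρ = 0.3 to 0.7 this runs from 0.832 to 0.997.

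At the assumed ρ of 0.5 the loss of power is small (0.957 to 0.943). The issue is who is analysed, more than how many.

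**4. Possible bias (illustration on assumed inputs)**

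There is no true effect and there are 20 participants per arm. The change score is standard normal, with higher values worse. In an arm with response-related dropout, each of the five worst responders leaves with probability 0.6. The result is the mean difference between arms among those analysed, averaged over 20,000 or more runs.

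| Scenario | Mean number lost | Mean difference |
|---|---|---|
| Same response-related dropout in both arms | 6 (3 + 3) | 0.00 SD |
| Response-related in one arm, five lost at random in the other | 8 (3 + 5) | about −0.22 SD |
| As above, leavers replaced by random draws | 8, replaced | about −0.18 SD |

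In the one-arm scenario the result depends on the assumed probability: about −0.10 SD at 0.3 and −0.41 SD at 1.0. A negative sign flatters the arm that lost its poor responders. The simulation covers only the comparison of group A with group B. It says nothing about the within-person comparison of active with sham.

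**The case against.** The best defence is that item 20c speaks of stopping treatment, while item 11b and the dropout definition speak of leaving the study. On that reading, someone who stops stimulation but still attends is analysed, and someone who leaves is not. This softens any claim that the two rules are incompatible in every case. It does not reconcile them: item 20c also covers those who refused, the article never draws the distinction, and a set that drops randomised study leavers is still not intention-to-treat.

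A reader might infer that the primary analysis will in fact be completers-only. The article does not support that. Item 20c is the section devoted to non-adherence and says the opposite, and the primary analysis text is silent. Completers plus replacements is what follows if item 11b is applied, not a stated decision.

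A reader might also take −0.22 SD as the expected bias. It arises only when response-related dropout is confined to one arm. Both groups receive ten active and ten sham sessions, and nothing in the article shows that leaving would differ between them. With like dropout in both arms the figure is 0.

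Three further points stand in the plan's favour. The 10 of 40 is a ceiling: the article elsewhere expects high compliance and little trouble with retention. Dropouts are to be registered, so the loss is recorded and not concealed. Replacing participants to hold the sample size is not in itself an error; the error is excluding the people who are replaced.

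That a separate analysis plan may exist does not remove the point. The protocol states two opposing rules, so a plan that follows either for study leavers contradicts the other.

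**Conclusion.** The concern holds as a contradiction that leaves the primary analysis set unfixed. It should be corrected, because it decides who enters the efficacy analysis and one of the two rules does not deliver the intention-to-treat analysis the protocol promises.

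The number affected is bounded by the planning ceiling, 10 of 40. The between-arm bias could be nil or about a fifth of a standard deviation under the assumptions shown, and it depends on whether leaving is related to response and differs between groups. The contradiction itself rests on no assumption: both rules are in the current text.

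**What to change.** - In item 11b, delete the sentence that excludes dropouts from the analysis.
- In item 20c and under Primary analysis, state that all randomised participants are analysed in their allocated group and sequence, and that the mixed model uses all data collected before withdrawal. Do not add a requirement for at least one post-baseline value to define the set: that is a modified set and would not match what item 20c promises.
- State that any replacements are additional randomised participants, not substitutes, and that those they follow remain in the analysis.
- A completers analysis may be kept, as a sensitivity analysis only.

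The cost is a change of wording and its notification to the ethics committee. It needs no new data, visits or participants.

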### Strategies to improve adherence to interventions {11c}

Participants will be contacted by phone and email, then appointments will be scheduled in advance according to the availability of each participant. In order to improve adherence, appointments will be available in three shifts, from Monday to Saturday.

The questionnaires will be collected on an easy-to-navigate online platform before each session at which the participants are present and in an online form in sessions 13 and 25. Additionally, after each therapy session, a safety questionnaire will be applied in order to identify any side effects resulting from the stimulation.

In case of non-compliance, such as absence in sessions, the participants will be contacted via telephone or email, and asked about continuation or early termination of the study.

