### Plans to promote participant retention and complete follow-up {18b}

No specific plans to promote participant retention are implemented in this trial. As this is a trial involving treatment for a symptom that so far has no cure, participant retention is not usually an issue in the treatment phase.

As the treatment is over an extended period of time, it is possible that sessions may be forgotten or forms not filled out and, in these cases, participants will be contacted by phone and email.

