### Adverse event reporting and harms {22}

Neuromodulation is a safe procedure, causing no apparent short- or long-term harm.

Only low adverse events are possible, such as headaches, burning, itching, tingling, tiredness, heat, redness, irritation, difficulty concentrating, and pain. However, the side effects will be monitored after each session through a safety questionnaire. In cases of the appearance of secondary effects to the treatment, the investigators are requested to report any untoward clinical event on the adverse event page of the case report form (CRF). All details will be reported, including the time of occurrence, symptoms and signs, severity, duration, and causal relationship with the treatment.

In case of discomfort to adverse events, the case will be analyzed by the health professionals involved, who will decide whether changes in the treatment could benefit the participants and reduce the side effects or whether participation in the study should be terminated.

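### The protocol promises intention-to-treat analysis of people who stop treatment, but its conduct rules do not separate stopping stimulation from leaving the study and secure no primary outcomes afterwards

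*Protocol article*

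**What the plan says.** All references are to the protocol article.

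- **Strategies to improve adherence {11c}.** Absent participants are to be "contacted via telephone or email, and asked about continuation or early termination of the study". Questionnaires are collected online "before each session at which the participants are present and in an online form in sessions 13 and 25".
- **Adverse event reporting {22}.** The health professionals decide "whether changes in the treatment could benefit the participants and reduce the side effects or whether participation in the study should be terminated".
- **Criteria for discontinuing {11b}.** The section foresees no realistic withdrawal scenario, but lets participants end participation at any time. Of those who do, it says: "They will be registered as dropouts and will not be taken into account in the analysis". They are replaced where possible. The one contact named is this: "After withdrawal, the participants will be contacted for a debriefing interview".
- **Participant retention and complete follow-up {18b}.** "No specific plans to promote participant retention are implemented in this trial". Retention is described as not usually a problem. Phone and email contact is foreseen for forgotten sessions and unfilled forms.
- **Protocol non-adherence and missing data {20c}.** Participants are analysed in their randomised arm "irrespective of whether they refused or discontinued the treatment, or whether other protocol violations occurred". Missing numerical values are filled with the mean over all participants, or by another imputation method if that fits better.
- **Sample size {14}.** 32 participants are needed. The target is 40 because a high dropout of up to 25% during treatment is expected.
- **Primary outcome {12}.** There are three measures: VAS loudness and VAS distress (self-report), and MML (measured).

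**The concern.** An intention-to-treat analysis of people who stop treatment needs their outcomes after they stop. That is a matter of trial conduct, and no analysis plan can recover values that were never collected. The conduct sections speak of continuing, changing the treatment or ending participation. None describes a participant who receives no further stimulation but stays in assessment, and none commits the team to obtaining a primary outcome from such a person.

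The article also holds two views of how often this will happen. The sample size section plans for a loss of up to a quarter during treatment, while the discontinuation and retention sections treat withdrawal as unlikely and plan little for it.

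At stake is the comparison itself. People who leave because of side effects or lack of benefit are likely to differ from those who finish. Excluding them, or giving them an average value, hides that difference. Replacement restores the head count but not their outcomes.

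**Working it through.** **1. The plan's own figure.** Inputs from Sample size {14}: f = 0.25, power 0.95 (labelled beta there), alpha 0.05, 2 groups, 5 measurements. The correlation between measurements is not stated; I assume ρ = 0.5 with sphericity.

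- Noncentrality: λ = f² × N × m / (1 − ρ) = 0.0625 × 32 × 5 / 0.5 = 20.
- Degrees of freedom: (2 − 1)(5 − 1) = 4 and (32 − 2)(5 − 1) = 120.
- Power is 0.957, and 32 is the smallest even N that reaches 0.95. The figure reproduces. With ρ = 0.3 the answer would be 44, and with ρ = 0.7 it would be 20.

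**2. Expected loss.** 0.25 × 40 = 10 leavers, so 40 − 10 = 30 remain before any replacement, two fewer than the 32 required.

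**3. Power, for scale only.** With f held unchanged:

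- N = 30: λ = 18.75, power 0.943 (0.832 at ρ = 0.3; 0.997 at ρ = 0.7).
- N = 40: λ = 25, power 0.987 (0.934 at ρ = 0.3; about 1.0 at ρ = 0.7).

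The second line is optimistic, because people who stop stimulation would dilute the effect. At ρ = 0.5, 30 participants fall only slightly short of the planned 0.95, so power is not the main problem.

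**4. Tracing a participant who stops.**

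- Misses sessions ({11c}): continue, or end the study early.
- Has an adverse event ({22}): treatment changed, or participation ended.
- Ends participation by choice ({11b}): registered as a dropout, not analysed, replaced where possible, debriefed.

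Primary-outcome questionnaires fall at the end of each block (sessions 11 and 23), at follow-up (12, 13, 24 and 25) and at close-out (26). For someone who has stopped stimulation, none of the three routes commits to any of these. Section {20c} nevertheless counts that person in the analysis. What it has available is its imputation rule, and {11b} excludes the person altogether if stopping is treated as leaving.

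**5. What dropping or mean-filling does.** Let p be the share with no outcome at a time point, and δ the difference between the leavers' true mean and the completers' mean.

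- Exclusion: the mean of all randomised is the completers' mean + p × δ, so the completers' mean is off by p × δ. At the ceiling p = 0.25 this is 0.25 × δ.
- Filling with a mean taken over both groups, with equal group sizes and equal p: each group mean becomes (1 − p) × own mean + p × overall mean. The group difference is then (1 − p) = 0.75 times the observed one at p = 0.25.

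The documents give no δ, so no bias figure follows. The value 0.25 is a ceiling, because the stated dropout is an upper limit and covers both blocks.

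**The case against.** **Inference from silence.** A reader might infer that stopping stimulation can only mean leaving, and that no primary outcome is ever collected afterwards. The documents do not say this. No section forbids assessment after stopping, {11c} allows continuation after absence, {22} allows treatment to be changed, and {20c} recognises people who stopped treatment. The debriefing follows withdrawal from the study, which is a different event from stopping treatment. The full protocol, not shown, may also give procedures that a journal article omits. This limits the point to what the article fails to separate and secure. It does not remove the point, because the article's own sections on discontinuation, adherence and follow-up take positions that do not fit {20c}.

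**Retention is not ignored.** The article foresees phone and email contact about missed sessions and unfilled forms, and offers appointments in three shifts from Monday to Saturday. This is true, and a reading that nothing is done would be wrong. These measures serve people who are still in the study.

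**A precision gain.** A reader might assume that half to 80% of the 10 leavers keep completing the VAS, giving 35 to 38 participants instead of 30. The standard error would then be √(30/35) = 0.926 to √(30/38) = 0.889 times as large, a fall of 7 to 11%. The documents do not support this. They give no basis for the retention share, leavers are to be replaced, people who leave in block 2 already have block-1 outcomes, and those who stop are not fully informative about active versus sham.

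**Limits of remote data.** VAS ratings without block-2 stimulation do not restore a within-person contrast of treatments actually received. That stands. They support an as-assigned comparison, which is what {20c} promises.

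**Conclusion.** The point holds as a mismatch between conduct and analysis. Sections {11b}, {11c} and {22} do not separate stopping stimulation from leaving the study, and no section secures primary outcomes after stimulation stops, while {20c} promises to analyse the people concerned. By the plan's own allowance this could affect up to 10 of 40 participants before replacement.

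The main consequence is bias. Its size is unknown, and its direction depends on why people leave. The conclusion assumes that some leave for reasons related to outcome. If leaving were unrelated to outcome, exclusion would cost mainly numbers, which replacement could restore, although filling with an overall mean would still shrink group differences.

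The exclusion in {11b} and the inclusion in {20c} also contradict each other. Resolving that on paper would not by itself produce the missing data. The matter should be corrected, and it can be corrected cheaply because two of the three primary outcomes are self-rated and remote online completion is already planned for sessions 13 and 25.

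**What to change.** Reconcile {11b}, {11c}, {18b} and {20c}:

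- Define stopping stimulation and withdrawing from the study as two separate events. This concerns data collection only; when stimulation is changed or stopped remains with the existing clinical provisions.
- Ask participants who stop stimulation or miss sessions, if they are willing and consent, to keep completing the online VAS for loudness and distress on the planned end-of-block, follow-up and close-out dates (sessions 11 to 13 and 23 to 26).
- Analyse these values in the randomised group under {20c}. Remove the exclusion in {11b} for anyone who has not withdrawn consent to data use.
- Bring the retention statement in {18b} and the withdrawal statement in {11b} into line with the 25% allowance in {14}.

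The cost is wording in the protocol and consent form, plus reminders through the online platform and the phone and email contact already planned. There are two downsides. Some data will come from partly treated participants and so estimate an as-assigned effect. MML will remain missing unless the person attends.
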